#### Sample size:

According to previous work presented in literature, we have estimated that a sample size of  $n = 130$  patients per randomized group, for a two-sided type I error at 5%, would provide 90% statistical power of detecting an absolute difference of 20% between ethosuximide and placebo in the primary outcome: rate of responders to treatment as defined previously (35% for placebo and 55% for ethosuximide). Finally, a total of  $n=290$  patients (145 by group) will be considered to take into account lost to follow-up (10%). An interim analysis will be performed after 100 included patients to analyse safety and effectiveness in order to recalculate the sample size according results.

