##### *Statistical methods*

Statistical analyses will be conducted using Stata software (version 13, StataCorp, College Station, US). A two-sided p-value of less than 0.05 will be considered to indicate statistical significance (except interim analysis).

Intent-to-treat (ITT), mITT, and per-protocol (PP) analyses were performed for the primary endpoint and expressed as relative risks (RR) with 95% confidence intervals (CI). Non-compliant patients were considered non-responders. Responder rates were compared using the chi-squared test and a pre-specified multivariate analysis was performed using a generalized linear mixed model (Poisson regression with a log link and robust variance 26) accounted for fixed covariates (e.g., gender, IBS subtype) and centre-level variability were performed. Primary endpoint components were also analysed with the Hochberg procedure for multiple testing.

Continuous outcomes were assessed with linear mixed models incorporating patient-level random effects (slope and intercept) nested within centre-level random effects. Results were expressed as regression coefficients (standardized mean differences - MD) with 95% CI, based on the interaction between time and randomization group. The normality of residuals from these models was analysed as aforementioned. Safety analysis was conducted with chi-squared or Fisher's exact tests.

Missing data (if any) were imputed using Multiple Imputation by Chained Equations (MICE). Analyses were conducted using Stata 15.0, with a two-sided P value <0.05 considered significant, and the widths of confidence intervals were not adjusted for multiplicity and should not be used as a substitute for hypothesis testing, except for the primary outcome and its composite components. An interim analysis is planned after enrolment of the first 100 patients using the Lan and DeMets rule (East software, Cytel Inc, Cambridge, Massachusetts, US). The type I error is fixed at 0.03 for this interim analysis. In addition, an early intermediate analysis (third of the inclusions) will be also proposed in order to study safety of the initial maximum dose (10 ml/day) and, if necessary, to allow the addition of a therapeutic dose in case of inefficiency.

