### 2.2 Study population

Intention-to treat (ITT) population: All randomised patients.

Because the study is a proof of concept, this population will not be analysed in the IBSET study.

Modified intention-to-treat population (mITT): All randomised patients except patients who:

- Patients who withdrawn consent for the use of data
- OR
- Patients who did not have any of the interventions
- OR
- Patients who did not be eligible for randomisation according to inclusion/non-inclusion criteria (screen fail or absence of baseline pain intensity [primary outcome])
- OR
- Patients with major deviation (primary outcome not available, non-compliance)

Per-protocol population: All randomised patients except patients having one or more major protocol violations defined as:

- Patients who accidentally received the wrong treatment
- OR
- Patients who discontinued study treatment
- OR
- Patients who did not have any of the interventions
- OR

- Patients who withdrawn consent for the use of data

OR

- Patients who did not be eligible for randomisation according to inclusion/non-inclusion criteria (screen fail or absence of baseline pain intensity [primary outcomes])

OR

- Patients with major deviation (primary outcome not available, non-compliance)

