Planned subgroup analyses were assess heterogeneity of the effect of ethosuximide on the primary outcome measure in pre-specified subgroups of patients with IBS subgroup and gender. According to usual recommendations, the interactions between group randomization and subgroups was evaluated in regression models (i.e., random-effects models, linear or generalized linear).

A descriptive analysis of stopping and discontinuations in view of dose escalation was considered. A particular focus was done to safety and lose to follow-up. A study of abandonment considered as censored data was proposed using the Kaplan-Meier estimation. The proportional-hazard hypothesis was verified using Schoenfeld's test and plotting residuals.

Finally, a sensitivity analysis was performed and the nature of missing data was studied (missing at random or not). According to this, the most appropriate approach to the imputation of missing data was proposed (MICE, spline interpolation, LOCF, BOCF...).

A two-sided P value of less than 0.05 was considered for statistical significance of all analyzes. The Hochberg procedure was used to adjust for multiple testing of each component of the composite primary outcome ((1) decrease of at least 30% of the intensity of abdominal pain (11-point NRS) compared with the score before treatment and (2) significant global improvement defined by a score of 4 or 5 on the SGA scale). Because of the potential for type 1 error due to multiple comparisons, findings from analyses of secondary endpoints were interpreted as exploratory.

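### The protocol and SAP give incompatible rules for missing week-12 outcomes and non-compliance, so the primary test is in effect complete-case and its sensitivity check is not fixed in advance

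*Combined protocol and SAP*

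**What the plan says.** **Protocol, Statistical methods.** ITT, mITT and per-protocol analyses are named for the primary endpoint. On missing data: "Missing data (if any) were imputed using Multiple Imputation by Chained Equations (MICE"). On adherence: "Non-compliant patients were considered non-responders".

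**Protocol, Data collection methods.** All patients are to be analysed by intent to treat, but after a major deviation only safety data are evaluated.

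**SAP 2.1 Generality.** The primary analysis is to be run in the ITT, mITT and per-protocol populations, before the randomisation code is broken.

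**SAP 2.2 Study population.** ITT is defined as all randomised patients, followed by a statement that it will not be analysed. Both the mITT and the per-protocol sets leave out "Patients with major deviation (primary outcome not available, non-compliance").

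**SAP 2.3 Primary analysis.** An unadjusted chi-squared (or Fisher's exact) test of responder rates, with no rule for a missing outcome.

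**SAP 2.4 Secondary analyses.** A sensitivity analysis is introduced, the nature of the missingness is to be examined, and on that basis "the most appropriate approach to the imputation of missing data was proposed (MICE, spline interpolation, LOCF, BOCF" or another method would be used. The list is left open. No decision rule, endpoint or population is given.

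**The concern.** The same patient is classed differently depending on the section read. A non-compliant patient is a non-responder in the protocol's statistical section and excluded under SAP 2.2. A patient without a week-12 pain score or SGA is imputed by MICE in the protocol, excluded under SAP 2.2, and handled by an unnamed method in SAP 2.4.

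This matters because dropout may well be related to arm. Treatment is titrated, and the protocol allows stopping or reduction for intolerance or for effectiveness (Treatment period 1). If more patients leave the ethosuximide arm because they cannot tolerate it, dropping them leaves a favourable subset in that arm.

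The check that should expose this is not fixed. Observed data cannot separate missing at random from missing not at random, so the trigger in SAP 2.4 cannot work as stated. The listed methods also rest on different assumptions:

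- BOCF gives zero pain change and hence non-response.
- LOCF can carry an early response forward.
- MICE treats dropouts like similar patients who stayed.
- A spline can fill intermittent gaps but has no later value to interpolate towards after dropout.

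**Working it through.** **Inputs.** From the protocol's sample size section: two-sided 5% error, 90% power, responder rates "35% for placebo and 55% for ethosuximide", 130 evaluable and 145 randomised per group, 10% loss with no split by arm. Dropout by arm below is assumed and is written ethosuximide/placebo.

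**1. The plan's own figure.**
n = [1.96√(2×0.45×0.55) + 1.282√(0.55×0.45 + 0.35×0.65)]² / 0.20² = (1.379 + 0.883)² / 0.04 ≈ 128. The stated 130 gives 90.5% power, and 130/0.90 = 144.4, rounded up to 145. The plan's figure is reproduced.

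**2. Complete-case test when there is no difference among all randomised.** Take 35% response in both arms of 145, with dropouts as non-responders. The rate among completers is then 0.35/(1 − dropout). Exact binomial probability that the chi-squared test gives p<0.05:

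| Dropout | Completers | Completer rates | Rejects |
|---|---|---|---|
| 10%/10% | 130 v 130 | 38.9% v 38.9% | 5.0% |
| 15%/10% | 123 v 130 | 41.2% v 38.9% | 6.5% |
| 15%/5% | 123 v 138 | 41.2% v 36.8% | 11% |
| 20%/10% | 116 v 130 | 43.8% v 38.9% | 12% |
| 25%/10% | 109 v 130 | 46.7% v 38.9% | 23% |

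**3. Does the method change the conclusion at the planning rates?** Take completer rates of 55% v 35% and an uncorrected chi-squared test, z = (p₁ − p₂)/√[p̄(1 − p̄)(1/n₁ + 1/n₂)]. Complete case stands in for MICE with no useful auxiliary variables. BOCF equals non-response, because a responder must meet the pain criterion.

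- Equal 10% loss: complete case 72/130 v 46/130, z = 3.24, p = 0.0012; non-response 72/145 v 46/145, z = 3.11, p = 0.0019. Same conclusion.
- 20%/10%: complete case 64/116 v 46/130, z = 3.12, p = 0.002; non-response 64/145 v 46/145, z = 0.124/0.057 = 2.18, p = 0.029. Still significant.
- 25%/10%: complete case 60/109 v 46/130, RR 1.56, z = 0.197/0.0645 = 3.05, p = 0.002; non-response 60/145 v 46/145, RR 1.30, z = 0.0966/0.0566 = 1.71, p = 0.088. Significance depends on the method. LOCF gives p = 0.031 if 20% of missing patients carry a response and p = 0.005 if 50% do.

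**4. When would the direction reverse?** Under non-response, 0.55(1 − m) < 0.35 × 0.90 requires m > 1 − 0.315/0.55 = 43% missing on ethosuximide, with 10% missing on placebo.

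**5. Power if missing counts as non-response.** With 145 per arm and completer rates of 55% v 35%, the compared rates are 49.5% v 31.5% at 10%/10% (power 88%), 44.0% v 31.5% at 20%/10% (59%) and 41.25% v 31.5% at 25%/10% (41%).

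**The case against.** The best defence is that the open list is confined to a sensitivity analysis in SAP 2.4. If patients without the outcome are excluded, imputation never reaches the primary test. SAP 2.1 places the analyses before code-breaking and SAP 1.5 blinds the statistician, so selection by treatment effect is limited. All of this stands.

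A reader might infer that a method picked after seeing the data could reverse the trial's result. The documents do not support that. At the planning rates with equal 10% loss the conclusion is the same, and a change of direction needs extreme imbalance. Nor is the 23% in the table inflation from choosing among methods. It is the error of one fixed complete-case analysis at one assumed split, and it comes from the exclusions in SAP 2.2. Picking the best of complete case, BOCF and LOCF under no effect, with equal missingness, gives 7.4% (10% missing per arm) to 8.4% (20% per arm) in simulation.

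Two further limits stand. MICE remains on the SAP list, so the conflict there is a fixed rule against an open choice. The protocol's non-responder rule names non-compliance, not missingness, and it is SAP 2.2 that contradicts it.

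The null in the table also assumes that dropouts truly are non-responders. If completers instead respond at 35% in both arms with 25%/10% missing, non-responder imputation itself rejects in about 17% of trials, nearly all favouring placebo. No single rule is neutral, which is why it must be fixed in advance and accompanied by named alternatives.

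The defence does not rescue the plan. If SAP 2.4 governs only a sensitivity analysis, the primary test is complete-case and its one robustness check is undefined. If SAP 2.1 prevails and ITT is analysed, SAP 2.3 has no rule for the missing outcomes.

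**Conclusion.** The point holds as a conflict between sections with a quantifiable consequence. Protocol Statistical methods, SAP 2.2 and SAP 2.4 cannot all be followed, and SAP 2.1 and 2.2 disagree on whether ITT is analysed. Followed as written, SAP 2.2 makes the primary comparison complete-case.

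The size depends on dropout by arm, which the documents do not give. There is no inflation at equal 10% loss. With ethosuximide dropout 5 to 15 points above placebo, the complete-case test rejects in 6.5% to 23% of trials with no difference, provided dropouts are non-responders. At the planning rates, complete case and non-response agree on significance at 10%/10% and 20%/10% and disagree at 25%/10%. This should be corrected before unblinding. It does not show that the trial's conclusion would be overturned.

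**What to change.** Before unblinding, align Protocol Data collection methods and Statistical methods with SAP 2.1, 2.2 and 2.4:

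1. Analyse the primary endpoint in all randomised patients, except those who withdrew consent for use of their data.
2. Count a missing week-12 NRS or SGA as non-response. Count non-compliant patients as non-responders, as the protocol already states.
3. Keep observed week-12 data for patients who stopped treatment. State whether stopping counts as non-compliance, and reconcile this with Treatment period 1, where stopping may follow effectiveness as well as intolerance. A blanket rule that everyone who stopped is a non-responder would conflict with that section.
4. In SAP 2.4, replace the open list and the data-dependent choice with two named sensitivity analyses: MICE by arm using the week 4 and week 8 values, and a tipping-point analysis that varies the response assumed for patients with a missing outcome.

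The cost is wording, one extra analysis and some power. With 145 per arm and completer rates of 55% v 35%, power is 88% at 10% loss in each arm, 59% at 20%/10% and 41% at 25%/10%. The last two figures mainly reflect that the difference among all randomised patients is then smaller than 20 points (12.5 and 9.75).
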